### **Visit 2 – Control for ASAT and ALAT at the patient's general practitioner (V2)**

Visit 2 will be performed one month after V1.

The patient's general practitioner will collect blood from the patient to determine creatinine, CK, ASAT, ALAT, and fasting blood glucose. Values will be transmitted to the local study site by fax.

[illegible]

| Visits                                            | Screening
(V0) | Baseline
(V1) | V2 | T1 | V3 | T2 | V4 | T3 | V5 | T4 | V6 |
|---------------------------------------------------|-------------------|------------------|----|----|----|----|----|----|----|----|----|
| Vital capacity                                    | X                 |                  |    |    |    |    |    |    |    |    |    |
| Status (El Escorial Criteria)                     | X                 |                  |    |    |    |    |    |    |    |    |    |
| Concomitant treatment                             | X                 | X                |    | X  | X  | X  | X  | X  | X  | X  | X  |
| Physical examination                              | X                 | X                |    |    | X  |    | X  |    | X  |    | X  |
| Weight                                            | X                 |                  |    | X  |    | X  |    | X  |    | X  |    |
| ALS FRS-R                                         |                   | X                |    | X  | X  | X  | X  | X  | X  | X  | X  |
| Euroqol EQ-5D                                     |                   | X                |    |    | X  |    | X  |    | X  |    | X  |
| Study drug delivery                               |                   | X                |    |    | X  |    | X  |    | X  |    |    |
| Drug accountability                               |                   |                  |    |    | X  |    | X  |    | X  |    | X  |
| Laboratory tests                                  | X                 | X                | X  |    | X  |    | X  |    | X  |    | X  |
| Pregnancy test
(serum HCG level or urine test) | X                 |                  |    |    |    |    |    |    |    |    |    |
| Compliance (pioglitazone level)                   |                   | X                |    |    | X  |    | X  |    | X  |    | X  |
| Compliance (asked for)                            |                   |                  |    | X  |    | X  |    | X  |    | X  |    |
| Adverse events                                    |                   | X                |    | X  | X  | X  | X  | X  | X  | X  | X  |

#### 5.4 *Unscheduled visits*

Unscheduled visits may be carried out at any time during the study in the case of a medical emergency, when a patient would like to report a medical problem or when the investigator considers this necessary for the patient's well being. These unscheduled visits must be recorded on the case report form. In no case must they lead to a modification in the study visits schedule stipulated by the protocol.

#### 5.5 *Visits following premature discontinuation of study treatment*

If a patient discontinues participation in the study for whatever reason, every effort has to be undertaken to perform an early termination visit. In this case, the same investigations have to be performed as in visit V6.

#### 5.6 *Sequence and duration of trial periods*

The duration of treatment will be 18 months resulting in a duration of the trial of about 24 months; 1 month will be reserved for screening, three for recruitment, 18 months for the treatment period, and two for an observational follow-up period after the interventional period. Then the functional and survival data will be analysed.

## 6 STUDY TREATMENTS

### 6.1 *Test preparations*

#### Investigative Products

##### Pioglitazone Tablets

|               |                                                                      |
|---------------|----------------------------------------------------------------------|
| INN:          | Pioglitazone                                                         |
| Trade name:   | Actos                                                                |
| Dosage:       | Tablets containing 15 mg, 30 mg, and 45 mg pioglitazone respectively |
| Daily dose:   | 1 tablet/day oral in the morning before breakfast                    |
| Manufacturer: | Haupt Pharma Brackenheim GmbH, Germany                               |
| Batch No.:    | See trial master file                                                |

##### Placebo (3 dosages for pioglitazone)

|              |                                                   |
|--------------|---------------------------------------------------|
| INN:         | Not applicable                                    |
| Trade name:  | Not applicable                                    |
| Dosage:      | Not applicable                                    |
| Daily dose:  | 1 tablet/day oral in the morning before breakfast |
| Manufacturer | Haupt Pharma Brackenheim GmbH, Germany            |
| Batch No.:   | See trial master file                             |

### 6.2 *Treatment packaging*

Haupt Pharma, Brackenheim/Germany will supply the study drugs. The study drugs will be packed in accordance with AMG. All drug supplies must be stored in accordance with the manufacturer's instructions and must be stored separately from normal clinic (study centre) stocks. The investigator shall be responsible for assuring that the study medication is stored in a dry location and not above 25 °C, protected from exposure to any environmental changes and is locked, so that only the investigator and specifically designated other persons can have access.

### 6.3 *Treatment labelling*

According to article 5 of the German GCP-V the labelling of investigational drugs contains at minimum the following information

Outer packaging

- Name and address of the Sponsor and the CRO
- Name and dosage of the test compound
- Lot-No.
- Formulation (e.g. tablet or capsule etc.)
- Content by weight, volume or number of units
- Administration route
- Expiry date
- Only for use in clinical trial
- Storage condition
- Keep away from children
- Contains lactose
- Patient ID
- Protocol ID, EudraCT No.
- Stratum (bulbar onset or spinal onset)

#### Blister

- Name and address of the Sponsor and the CRO
- Lot-No.
- Protocol ID
- Patient ID
- Administration route

### **6.4 Storage of drug supplies**

The study drug will be directly sent to the study site. The investigator will confirm receipt of the first and all subsequent batches of study drugs in writing to Haupt Pharma Brackenheim GmbH. All drug supplies must be stored in accordance with the manufacturer's instructions, and separately from normal clinic (study centre) stocks. At the study site, the investigator is responsible for assuring that the study medication is stored properly, protected from exposure to any environmental changes and is locked, so that only the investigator and specifically designated other persons can have access.

## **6.5 Treatment assignment**

The investigator must only give the study treatments to the patients included in the trial according to the procedures stipulated by the protocol. It is strictly prohibited to use these treatments for any other reason than that described in the protocol. The medication will be given to the patient directly by the investigator. If the patient misses a visit, the medication can be given to a relative or can be sent.

## **6.6 Treatment administration**

Pioglitazone (oral 15 to 45 mg /day; uptake: 1-0-0, before breakfast; tablets include 15, 30 or 45 mg pioglitazone)

### **V1 (Baseline):**

- A) 1 blister with 14 tablets pioglitazone 15 mg,  
1 blister with 14 tablets pioglitazone 30 mg,  
2 blister with 14 tablets pioglitazone 45 mg
- B) 1 blister with 14 tablets placebo matching pioglitazone 15 mg,  
1 blister with 14 tablets placebo matching pioglitazone 30 mg,  
2 blister with 14 tablets placebo matching pioglitazone 45 mg

### **V2 (Month 1):**

No study drug delivery, medication included in V1 package

### **V3 (Month 2):**

- A) 8 blister with 14 tablets pioglitazone 45 mg
- B) 8 blister with 14 tablets placebo matching pioglitazone 45 mg

### **V4.1 (Month 6), V4.2 (Month 9), V5.1 (Month 12), V5.2 (Month 15):**

- A) 6 blister with 14 tablets pioglitazone 45 mg
- B) 6 blister with 14 tablets placebo matching pioglitazone 45 mg

### **Medication for reserve (two packages: one for V1, one for V4.2)**

- A) 2 blister with 14 tablets pioglitazone 45 mg
- B) 2 blister with 14 tablets placebo matching pioglitazone 45 mg

## **6.7 Overdose**

There is no specific advice in case of an overdose. General measures should be taken.

## **6.8 Compliance**

The investigator will select patients who have the ability to understand and comply with instructions for trial participation. Non-compliant participants will be dropped from further participation in the trial. Compliance of the patient will be judged by the investigator. Additionally, the study drugs will be dispensed exclusively by the investigator or a designate. All unused study medication will be returned to the investigator. Drug accountability including tablet counts will be performed by the investigator.

Patients will be asked to return their unused study medication including the empty blisters and boxes at each visit. To assess compliance, the remaining tablets will be counted out of the patient's presence. At visit V1, V3, V4, V5, and V6 pioglitazone levels will be measured in the serum of each patient to control compliance. Patients, who have taken more than 120% or less than 80 % of the medication during the treatment period, may continue the trial but will not be included in the per protocol analysis.

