### 6.10.3 Emergency procedure for unblinding

Each study site will receive sealed unblinding envelopes for emergency cases. Haupt Pharma Brackenheim will send the envelopes to the sites together with the matching medication.

In case of an emergency situation the investigator has the right to open the unblinding envelope, but every effort should be taken to avoid unblinding of patients except the information will be needed for the emergency treatment. Opened envelopes have to be signed, dated and the reason for unblinding has to be documented. The envelope has then to be filed in the patient file and the sponsor or the responsible monitor has to be informed. Unblinded patients have to be withdrawn from the study.

Additionally the sponsors' safety contact will receive a full set of sealed unblinding envelopes for emergency cases. As well every effort should be taken to avoid unblinding of patients except the information will be needed for the emergency treatment. Opened envelopes have to be signed, dated and the reason for unblinding has to be documented.

No other reason than an emergency may justify unblinding. After unblinding the investigator must note the date, time and reason on the case report form. The investigator must also immediately inform the trial monitor of the breaking of the blind.

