## **7.6 Premature discontinuation / Patient replacement**

Each patient can at any time withdraw from the study without personal disadvantages and without stating reasons.

Whenever possible, all patients prematurely discontinuing study medication will continue to be followed and complete all scheduled evaluations for the duration of the study. The reason(s) for premature cessation of a patient's participation during the trial, other than death, should be specified on the case report form. Whenever possible the evaluations scheduled for the end of the treatment period should be performed.

Study treatment may be stopped prematurely if any of the following events occur, according to the judgement of the investigator:

- Significant intolerance of the study medication, or significant clinical or laboratory findings, e.g. increase in ASAT or ALAT >2.5 upper limit of normal
- Significant intercurrent illness or emergency situation requiring cessation of the study
- The patient wishes to terminate his/her participation in the study
- Investigator judgement that it is in the best interest of the patient
- Failure to comply with the investigational procedures
- Pregnancy
- Technical reasons (change of physician, change of address of volunteer/patient)

Patients who have started double-blind treatment will not be replaced.

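### Sections 6.8 and 6.10.3 remove non-compliant and unblinded patients from the trial, against the follow-up rule in section 7.6, so deaths may be lost to the primary survival analysis

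*Protocol*

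**What the plan says.** Protocol section 6.8 states "Non-compliant participants will be dropped from further participation in the trial" and, directly after, "Compliance of the patient will be judged by the investigator". No threshold is attached to that rule. The same section ends by treating intake outside 80-120% differently: such patients "may continue the trial but will not be included in the per protocol analysis". It also provides that at V1, V3, V4, V5 and V6 "pioglitazone levels will be measured in the serum of each patient to control compliance".

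Section 6.10.3 adds a second removal rule: "Unblinded patients have to be withdrawn from the study".

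Section 7.6 points the other way: "Whenever possible, all patients prematurely discontinuing study medication will continue to be followed and complete all scheduled evaluations for the duration of the study". Its list of reasons for stopping study treatment early includes failure to comply with the investigational procedures.

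Section 5.5 asks for an early termination visit when a patient ends participation. Section 7.6.1 adds, where possible, a visit two weeks later. Section 5.3 bars re-entry. Nothing requires vital status beyond that for a patient who has left.

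The primary endpoint is death (section 3). It is tested by log-rank (8.2.5) in the full-analysis set, that is, randomised patients with at least one dose (8.2.1).

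**The concern.** A site with a non-compliant patient has instructions that cannot all be followed: remove the patient from the trial, let the patient continue, or stop treatment and keep following. For an unblinded patient, removal is mandatory.

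Removed patients stay in the full-analysis set. If removal ends follow-up, their survival time can only be censored at that date. The log-rank test assumes that censoring carries no information about the risk of death. That is doubtful here: emergency unblinding happens in emergencies, and non-compliance can accompany decline or side effects. Deaths that sites were told not to follow may be unrecoverable later, and no analysis plan can repair that.

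**Working it through.** **1. The rules side by side**

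| Situation | Section | Instruction |
|---|---|---|
| Non-compliant, investigator's judgement | 6.8, opening | Removed from the trial |
| Intake outside 80-120% | 6.8, end | May stay; leaves the per-protocol set only |
| Failure to comply | 7.6 | Reason to stop treatment; follow-up continues whenever possible |
| Emergency unblinding | 6.10.3 | Withdrawn from the study |
| Leaves participation | 5.3, 5.5, 7.6.1 | Termination visit, possibly one more at two weeks; no return |

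The conflict is direct for non-compliance. For unblinding it is slightly weaker: 7.6 does not list unblinding, but a patient withdrawn from the study also stops study medication and so falls under its follow-up rule.

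**2. The plan's own figures reproduce (inputs from 8.1)**

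- HR = ln(0.78)/ln(0.60) = 0.486.
- Boundaries 2.797 and 1.977 at information 0.5 and 1: crossing probability = 1 − P(Z1 < 2.797, Z2 < 1.977), correlation √0.5, means θ√0.5 and θ. With θ = 0 this gives 0.0250. With θ = |ln 0.486|·√61/2 = 2.81 it gives power 80.1%.
- Expected deaths: with 6 months' uniform accrual and 21 months in total, the probability of death is 1 − [exp(−15λ) − exp(−21λ)]/(6λ). For λ = −ln(0.60)/18 = 0.0284 this is 0.399. For λ = −ln(0.78)/18 = 0.0138 it is 0.220. Then 198 × (0.399 + 0.220)/2 = 61.3 deaths.
- 198/0.90 = 220 patients.

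**3. Equal loss in both arms**

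- 220 patients give 220 × 0.3095 = 68.1 deaths at 21 months. Losing 10% leaves 68.1 × 0.90 = 61.3, with power 80%.
- The apparent HR of a null drug is 0.90/0.90 = 1, so type I error stays at 2.5%.

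**4. Unequal loss (the shares are assumptions; the protocol gives none)**

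Apparent HR of a null drug = (1 − share lost on pioglitazone)/(1 − share lost on placebo). θ = −ln(HR)·√61/2, put into the crossing probability above.

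| Deaths lost, pioglitazone vs placebo | Apparent HR | θ | One-sided type I error |
|---|---|---|---|
| 10% vs 10% | 1.000 | 0 | 2.5% |
| 10% vs 5% | 0.947 | 0.21 | 4.0% |
| 15% vs 5% | 0.895 | 0.43 | 6.3% |
| 20% vs 5% | 0.842 | 0.67 | 9.8% |
| 5% vs 15% | 1.118 | −0.43 | 0.8% |

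**5. Check by simulation**

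Set-up: 220 patients, a single log-rank test at 1.96. A share of the patients who would die is withdrawn 0-3 months before death and censored then.

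- No drug effect, equal shares of 5% or 10%: type I error 0.024-0.027.
- No drug effect, 15% vs 5%: 0.069. 20% vs 5%: 0.111. 5% vs 15%: 0.007.
- Design HR, 10% vs 10%: power 0.79, against 0.83 with no removal.

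The mechanism matters. In a second model, 15% vs 5% of patients were removed at random times and their hazard tripled afterwards. Censoring at removal then left type I error at 0.026 and the apparent HR at 1.00. Continued follow-up gave 1.07. There the censoring hid an excess of deaths in the arm with more removals instead of producing false positives.

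**The case against.** The strongest reply is that the protocol never says survival is censored at removal. Section 7.6 could be read as governing, the endpoint is a date of death supported by a death certificate (5.2), and the handling of missing data is left to the analysis plan (8.3), which is not at hand. This stands in part: the informative censoring is an inference from the removal wording. It does not settle the conflict, because 6.8 and 6.10.3 are worded as removal from the trial or study, and 7.6 says only whenever possible.

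Three stronger readings are tempting and not supported.

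- **Power falls to about 76%.** That figure comes from taking 10% off 61 deaths (54.9). It ignores the 220 patients enrolled to allow for 10% drop-out. The final analysis is also triggered by the number of deaths, so a moderate loss mainly delays it.
- **The type I error is 6.3% or more.** This needs unequal loss in a particular direction. Equal loss gives no inflation, and the reverse split makes the test conservative.
- **Serum levels reach sites, unblind them and make the dropping rule act on one arm only.** Placebo patients cannot show drug, so a level seen at a site could unblind, and an absent level could expose non-compliance only on pioglitazone. But nothing says that results return to sites or inform the decision to drop. Section 8.2 treats serum concentrations as data to be summarised. The gap is that the recipient is not stated.

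Nor does the protocol show that the removed patients are the ones deteriorating. Section 5.1 provides for crushed tablets by feeding tube, so loss of swallowing need not mean non-compliance.

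**Conclusion.** Wrong as written. The contradiction among 6.8, 6.10.3 and 7.6 rests on the text alone. It bears on ascertainment of the primary endpoint, because patients removed under those rules have no required vital-status follow-up.

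The statistical consequence is conditional. It assumes that removal ends follow-up and that removal is related to prognosis. The number of patients affected is unknown. With equal loss, type I error stays near 2.5% and the enrolment allowance absorbs a 10% loss of deaths. With unequal loss, the bias can go either way: about 6.3% one-sided type I error at an assumed 15% vs 5% (pioglitazone vs placebo), about 0.8% at 5% vs 15%. None of the sample-size figures in 8.1 is wrong.

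**What to change.** Reconcile 5.3, 5.5, 6.8, 6.10.3 and 7.6 by separating two events: stopping study drug and leaving the study.

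- Reword 6.8 and 6.10.3 so that neither non-compliance nor unblinding ends follow-up.
- State once that vital status is collected to the end of the planned observation period for every patient in the full-analysis set, unless the patient withdraws consent to follow-up, and that these deaths count in the primary log-rank test. This changes neither the definition of the full-analysis set nor the observation period.
- State that serum pioglitazone results are withheld from sites until database lock, because a detectable level would unblind.

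Whether study drug continues in non-compliant or unblinded patients is for the sponsor to reconcile; this point takes no position on it.

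The cost is protocol wording, a restricted flow of laboratory results and a few extra telephone contacts. Telephone contacts (5.3) and death certificates (5.2) are already part of the trial.

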### 6.10.2 Blinding

Blinding of investigator and patient is achieved by providing pioglitazone and matching placebo tablets.

The randomisation list is kept confidential by Haupt Pharma Brackenheim, Germany, and is only accessible to authorised personnel until the code is broken. At the end of the trial, any emergency opening of the envelopes will be controlled after collecting the explanations for unblinding and checking the unused treatment units. The code will be broken only at the end of the study after freezing the statistics database (by checking the data, recording any protocol violations etc.) allowing the collected data to be analysed.

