## 8.2 Statistical methods

A Statistical Analysis Plan describing all details of the analyses to be performed will be prepared by the study statistician and approved by the sponsor prior to the start of statistical analysis. The recommendations of the ICH E9 Note for Guidance on Statistical Principles for Clinical Trials (CPMP/ICH/363/96, 1998) will be taken into account.

The primary endpoint will be subjected to a confirmatory analysis. All secondary and safety parameters will be evaluated and reported descriptively.

All individual data as well as results of statistical analyses – whether explicitly discussed in the following sections or not – will be presented in individual subject data listings and statistical summary tables.

Continuous variables will be summarised using the following standard descriptive summary statistics: number of observations, arithmetic mean, standard deviation, minimum, lower quartile, median, upper quartile, maximum. In addition, geometric mean and coefficient of variation derived from log-normally distributed data will be calculated for serum concentrations. Categorical data will be described using absolute and relative frequencies.

A more detailed elaboration of the principal statistical features stated in this protocol will be provided in the statistical analysis plan, which will be finalized prior to unblinding of the database. The statistical analysis plan will take into account any amendment to the study protocol.

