### 8.2.1 Populations

The following data sets will be analysed:

- Full-analysis set:

All randomised patients who received at least one dose of study medication will be included in the all patients treated set.

- Per-protocol analysis set:

The per protocol analysis set will consist of all patients in the full analysis set without any major protocol violations. Patients with major protocol violations will be excluded from the per-protocol analysis. The classification of major and minor protocol deviations and the resulting definition of analysis sets will be performed prior to the final analysis and will be approved by the sponsor.

All analyses with respect to safety and tolerance will be performed for the full-analysis set. All efficacy analyses will be conducted for the full-analysis set and for the per-protocol analysis set. The primary data set for the efficacy analysis will be the full-analysis set.

A more detailed description of the criteria used for data sort out will be included in the statistical analysis plan before start of the evaluations prior to unblinding the treatment allocation.

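### Serum pioglitazone is measured to control a compliance judgement made by the blinded investigator, and no stated rule keeps the results from sites or blinded staff

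*Protocol*

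**What the plan says.** Section 6.8 of the protocol brings three things together.

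- The decision and who makes it: "Non-compliant participants will be dropped from further participation in the trial. Compliance of the patient will be judged by the investigator".
- The measurement: "At visit V1, V3, V4, V5, and V6 pioglitazone levels will be measured in the serum of each patient to control compliance". V1 is a baseline sample taken before the first dose, so the on-treatment levels are those at V3 (month 2), V4 (month 6), V5 (month 12) and V6 (month 18). Both schedule tables label the test as a compliance measure, and Table 5.1 lists it among the safety bloods.
- A second rule, on medication taken: patients above 120% or below 80% "may continue the trial but will not be included in the per protocol analysis".

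The investigator is also expected to use drug levels elsewhere. In 7.3.1, a toxic concentration is one of the findings that can support a definite causal relationship. In 7.3.2, drug levels are among the points to be weighed in judging causality.

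On the blind, 6.10.2 says: "Blinding of investigator and patient is achieved by providing pioglitazone and matching placebo tablets". It also keeps the randomisation list confidential, has emergency envelope openings checked, and defers the code break until the database is frozen. Section 6.10.3 allows unblinding only in an emergency and requires unblinded patients to be withdrawn.

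On analysis, 8.2 says that a "coefficient of variation derived from log-normally distributed data will be calculated for serum concentrations", and 8.2.1 says: "The classification of major and minor protocol deviations and the resulting definition of analysis sets will be performed prior to the final analysis".

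**The concern.** In a placebo-controlled trial, the serum level of the study drug is close to a statement of allocation. Section 6.8 names that level as a tool for controlling compliance, and compliance is judged by someone who must stay blind and whose judgement can end a patient's participation. The same person assigns causality, scores ALSFRS-R and is close to decisions on ventilation. If the results reach that person, these decisions can differ by arm for reasons unrelated to the drug's effect. If the results reach the people who classify protocol deviations, the per-protocol set can be shaped with knowledge of the arm. The protocol's own standard, that only an emergency justifies unblinding, shows how seriously it takes routine disclosure.

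**Working it through.** The plan gives no figure on this point. The design figures are not affected: the hazard ratio is ln(0.78)/ln(0.60) = 0.486; Schoenfeld's formula at one-sided 0.025 and 80% power gives 60.4, rounded up to 61 deaths as stated; and 198/(1 − 0.10) = 220 as stated. The check is therefore mainly textual.

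**Step 1. Does the level carry allocation?** Placebo patients receive no pioglitazone. Section 4.3.2 excludes thiazolidinediones in the three months before screening and other antidiabetics, and 6.9 does not allow medication listed in the exclusion criteria during the trial. A detectable level at V3 or later therefore points to the active arm, assuming a specific assay. An undetectable level fits either placebo or a treated patient who is not taking tablets. With a good tablet count, it points to placebo.

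**Step 2. How informative is an undetectable level on its own?** Allocation is 1:1 (110 and 110). Let a be the probability that a pioglitazone patient has a detectable level. The protocol gives neither an assay limit nor an adherence rate, so a is assumed and shown over a range.

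P(placebo | undetectable) = 0.5 / (0.5 + 0.5(1 − a))

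Share of all patients undetectable = 0.5 + 0.5(1 − a)

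| a (assumed) | P(placebo given undetectable) | Share undetectable |
|---|---|---|
| 1.00 | 1.00 | 50% |
| 0.95 | 0.95 | 52.5% |
| 0.90 | 0.91 | 55% |
| 0.80 | 0.83 | 60% |
| 0.70 | 0.77 | 65% |

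Before the result, the probability is 0.50. Even at a = 0.70 it rises to 0.77 before the tablet count is considered.

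**Step 3. Is the result tied to blinded decisions?** Yes, by stated purpose. Section 6.8 says the level controls compliance and that "Compliance of the patient will be judged by the investigator"; 7.3.1 and 7.3.2 bring drug levels into the investigator's causality assessment.

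**Step 4. Is there a barrier?** None of the safeguards in 6.10.2 and 6.10.3 covers assay results. The access restriction in 10.2.2 concerns unblinded and interim data held by the DMSC and the unblinded statistician. No readable section says that levels are assayed after the freeze or sent only to an unblinded party.

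**Step 5. Which results are exposed?** The primary endpoint is death, documented by certificate, so assessment bias there is small. What remains for the primary analysis is arm-dependent dropping and hence censoring. Section 7.6 limits this by following patients who stop medication whenever possible. More exposed are ventilation decisions, ALSFRS-R, EQ-5D, adverse event causality and the per-protocol classification.

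**Step 6. Are the compliance rules in 6.8 consistent?** No. One statement is "Non-compliant participants will be dropped from further participation in the trial"; the other lets patients outside 80–120% stay in the trial and excludes them only from the per-protocol analysis. The text does not say how the two fit together.

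**The case against.** The strongest reply is that delivery of the results to the investigator is an inference. Section 6.8 names no recipient, timing, threshold or action for the levels, and a central assay read after the freeze would fit the sentence. Part of the visit text in 5.3 after V2 is unreadable and may contain handling instructions. This stands, and it is why unblinding is put as a risk.

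A reader might infer that all placebo patients would count as non-compliant and be dropped. The documents do not support that. There is no level-based criterion: 6.8 counts tablets and sets its limits on medication taken, and 8.2.3 computes compliance from dispensed and returned medication.

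A reader might also infer that every allocation becomes known at V3. An undetectable level alone is not proof, as the table above shows.

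Nor does it follow that the levels sit in the database when deviations are classified. Section 8.2 says only that they are summarised, 8.2.1 leaves detailed criteria to the SAP, and 8.3 refers to a Data Management Plan. Neither plan is shown.

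Finally, one might try to count placebo deaths lost through selective dropping. The protocol gives no drop rate for such a count, 8.1 expects under 1% loss to follow-up, and the 61-death target is derived from 99 patients per arm, not 110. No such figure is supportable.

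The reply does not remove the conflict in the stated text: an allocation-revealing measurement serves a blinded person's judgement, and causality guidance directs that person to drug levels. This is more than operational detail left to another document.

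**Conclusion.** The point holds as a blinding weakness that should be corrected. Following 6.8, 7.3.1 and 7.3.2 as written can place treatment-revealing results in front of investigators, and nothing readable prevents it. Whether that would happen cannot be settled from the protocol.

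The size is qualitative. No sample size, critical value or event count changes. The probability range of 0.77 to 1.00 for placebo given an undetectable level assumes 1:1 allocation, a specific assay, no outside source of the drug, and 70% to 100% detectability in treated patients. The effect on the primary comparison is limited to possible arm-dependent dropping and censoring. The secondary endpoints, which are descriptive, and the per-protocol set, which is not the primary set, are more exposed.

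**What to change.** - In 6.8, state that compliance during the trial, including the 80–120% rule, is judged on tablet counts. This agrees with 8.2.3.
- In 6.8 and 6.10.2, state that the laboratory releases no pioglitazone level to sites, monitors, data management or blinded statisticians until the code is broken. The unblinded statistician working for the DMSC may receive them.
- State that levels are not used in the blinded review of protocol deviations and analysis sets under 8.2.1, and are merged for the summaries in 8.2 only after the code break.
- Align the references to drug concentrations in 7.3.1 and 7.3.2 with this restriction.
- Reconcile the two statements in 6.8 on what happens to non-compliant patients.

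The cost is wording and a laboratory instruction. The sampling schedule and blood volumes stay as they are. The downside is that sites have no real-time level results.
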